## Abstract

**Background:**

Grief reactions of relatives of palliative care patients are seldom addressed. Most interventions focus on Prolonged Grief Disorder (PGD) and not on its prevention. This is particularly relevant in palliative care, in which death is the result of a difficult period of a terminal illness, making caregivers particularly vulnerable to psychological distress. The purpose of the present exploratory trial is to test the efficacy of a selective intervention (Empower-Grief) for the initial problematic grief reactions and to study potential predictors of adherence and efficacy.

**Method:**

This is an exploratory Randomized Controlled Trial (RCT) studying Empower-Grief compared with Treatment as Usual (TAU). Participants will be relatives or caregivers of palliative and oncological patients with initial indicators of risk of developing PGD and will be randomly allocated to Empower-Grief and TAU. Participants will be assessed prior, at the end and six months after the intervention. The primary outcome considered will be symptoms of PGD. The assessment includes measures of anxiety and depression, coping, attachment, psychological flexibility, posttraumatic growth, social support and therapeutic alliance.

**Results:**

The trial is ongoing. Forty-four participants will be invited to participate.

**Conclusion:**

This study addresses the need for the development of empirically grounded and feasible interventions aimed at dealing with initial problematic reactions in grief, exploring potential predictors and possible venues for personalizing intervention and understanding the mechanism through which these interventions operate.

## Background

Prolonged Grief Disorder (PGD), recognized as a mental illness in the ICD-11 (World Health Organization, 2019) and more recently in the DSM-5-TR (American Psychiatric Association, 2022), consists of intense grief along with significant social and occupational dysfunction persisting for an extended period (with the inclusion in the DSM-5-TR, the temporal criterion was extended from 6 to 12 months).

Caregivers of patients with advanced cancer are particularly vulnerable to elevated psychological distress. In a caregiver sample, PGD prevalence was 40% at six months, 28% at 13 months, and 27% at 18 months (Guldin et al., 2012), thus supporting the idea that end-of-life caregiving increases the risk of mental health disturbance. High levels of PGD were also found in a Portuguese population of palliative care caregivers (Coelho et al., 2022).

Considering the elevated prevalence of disordered reactions, the goal of providing different interventions according to the risk of developing PGD has the potential to provide care to more individuals. These interventions range from psychoeducation (i.e., universal interventions) to low-intensity selective and high-intensity indicative interventions. Very few low-intensity interventions have been proposed. Lichtenthal and colleagues (Lichtenthal et al., 2022) developed a brief manualized cognitive-behavioural, acceptance-based intervention for critically ill patients´ caregivers called EMPOWER (Enhancing and Mobilizing the POtential for Wellness and Resilience). EMPOWER is a psychological intervention composed of six modules based on cognitive-behavioural and acceptance-based interventions: 1) initial assessment, rationale and adherence to the intervention; 2) resources for stabilization; 3) psychoeducation on grief and the cognitive-behavioural model; 4) promoting experiential acceptance; 5) imagined dialogue; 6) coping training. This intervention has been shown to be feasible, acceptable and effective in reducing psychological symptoms, including PGD, depression and anxiety. This program, designed initially for intensive care contexts, emphasizes the detrimental role of experiential avoidance (i.e., the tendency to avoid unpleasant feelings) in decision-making and the grieving process. As opposed to acceptance, this coping mechanism has been associated with higher anticipatory grief (Davis et al., 2017) and the persistence of complicated grief in palliative care (Eisma & Stroebe, 2021).

The majority of the family caregivers will require selective intervention, oriented at people identified as being at risk of developing PGD. The differentiation of interventions allows combining need-based timely interventions to prevent PGD while increasing access through rationalization of service delivery. Despite the recommendations, no studies have matched the intensity of interventions to the severity of psychological reaction to death in preventing prolonged grief. The present research intends to implement and evaluate the effectiveness of the Empower-Grief intervention (Coelho et al., 2024; Lichtenthal et al., 2022) in the population of family caregivers of patients accompanied in the Palliative Medicine Unit of the Centro Hospitalar Universitário Lisboa Norte (CHULN). Empower-Grief is an adaptation of the original EMPOWER to the current palliative care context and post-mortem stage. It consists of the same six modules of the original intervention, but a 50-minute session is devoted to each of the modules, with two booster sessions done after treatment. It is a manualized treatment in which each session is structured.

This research project has two objectives. First, to evaluate the effectiveness of Empower-Grief Intervention compared to treatment as usual (TAU) in terms of symptoms of prolonged grief and psychological distress in relatives or caregivers of palliative and oncological patients. The second objective is to identify predictors, among the factors consistently found in the literature, of response to intervention. This second objective is crucial, considering the low-intensity level of the intervention. In addition to the risk of prolonged grief, other factors such as prior mental health, the nature of the death, social support, attachment style and psychological flexibility may be relevant in explaining the response to this intervention and serve as essential variables in adapting the intervention to the needs of the participants. This research is crucial to influence national policy towards a greater emphasis on prevention and early intervention, making the allocation of cost-effective bereavement support services the most efficient and sustainable approach for a significant public health impact in bereavement care.

## Method

### Design

The present study is an exploratory Randomized Controlled Trial (RCT) with two parallel groups (Figure 1) comparing the experimental treatment conditions, Empower-Grief, and treatment as usual (TAU) in a medical centre. All study procedures have been approved by the local and central institutional review boards. The project was approved by the ethics committee of ISPA (I-138-2-24).

### Setting and Participants

Treatment is offered at CHULN Lisboa Norte to family members or other caregivers of patients, followed by the palliative care unit and oncology service. Inclusion criteria involve individuals more than 18 years old, having experienced the death of a close person (e.g., relative, partner, friend) due to cancer in a palliative or oncological context from three to 12 months, and sufficient cognitive abilities and proficiency in the Portuguese language who provide written informed consent. Participants are invited from the service registry, where the reference caregiver is identified. Exclusion criteria include individuals reporting a diagnosis of pre-existing severe or active mental disorder predating the loss (e.g., schizophrenia, bipolar disorder, major depression). Participants currently undergoing psychological intervention will also be excluded. While medication will be monitored, it will not be an exclusion criterion.

### Recruitment, Enrollment, and Randomization

Family members will be contacted by phone from the CHULN. The number of participants who refuse to participate, change their address, or are unreachable will be registered. Unreachable participants are considered those who are not reached after one month of attempts. Second, the protocol of contact is established and will be revised to address any concerns participants may have. Non-participation data will be controlled monthly (weekly at the beginning of the data-gathering period).

Participants will undergo assessment for PGD risk and then be randomly assigned to one of the two conditions. Those considered at risk, using the cut-off values (i.e., 7 or more) of Risk Assessment for Grief (Ministry of Health, 2017) to be at a moderate level, will be invited to additional intervention and participation in the current study. All participants will provide informed consent before initiating one of the two interventions. The informed consent process will cover the study's purpose, procedures, potential risks, and benefits, and it will be obtained from each participant before any data collection or randomization occurs. Participants will be informed that their data will be anonymized and securely stored.

The analysis follows an intention-to-treat principle, ensuring the inclusion of every randomized participant. Participants who do not meet the criteria will be carefully referred to an appropriate service. In cases where participants refuse, do not adhere to, or do not benefit from a particular intervention, they will be offered the intervention at a higher level in the referred services.

Randomization is independently conducted by a research assistant. Participants will be randomly assigned to Empower-Grief vs. TAU. Randomization occurs after a participant meets eligibility criteria, provides consent, and undergoes risk assessment. A random sequence of numbers or allocation codes will be generated using a randomization tool. This sequence will determine the allocation of participants to the two intervention groups. The participants will be allocated to each branch of the RCT through block randomization. Clinicians will not be aware of any research assessments, including the initial risk assessment, and will not be involved in assessing participants' outcomes.

Throughout the study, the project team will continuously monitor the randomization process to ensure it is executed as planned, with any deviations documented and addressed. The study protocol was written in accordance with the SPIRIT 2013 Statement (Standard Protocol Items: Recommendations for Interventional Trials (Chan et al., 2013).

Strategies to enhance participant retention and minimize attrition will be employed, including regular check-ins, reminders for follow-up assessments, and flexible scheduling options. Also, a feedback system for participants to express concerns or provide input on the study's procedures will be put in place, and this will be used to make necessary adjustments. Throughout their participation, we will emphasize participants’ contribution to improving grief support for others and the rigorous privacy and confidentiality measures in place.

### Treatment Conditions

#### TAU

Treatment as usual (TAU) consists of supportive psychotherapy based on a non-structured and integrative method that focuses on developing more adaptive coping strategies and understanding and working on the patient's internal models of self, others, and the world (Winston & Lujack, 2015). For the present investigation, TAU will be considered during the same period as the Empower-Grief intervention – that is, 12 weeks – as the frequency of sessions may differ slightly from case to case. Psychologists with specific training for each intervention will administer both interventions.

#### Empower-Grief

Empower-Grief (Coelho et al., 2024) is a cognitive-behavioural and acceptance-based intervention divided into six modules adapted from EMPOWER (Lichtenthal et al., 2022) to a post-mortem application. It consists of six in-presence or online 50-minute sessions and two booster sessions 2 and 4 weeks after the final intervention. It is a manualized treatment in which each session has a specific goal: 1) Welcome, initial assessment and adherence to the intervention; 2) Psychoeducation and transmission of resources for stabilization; 3) Psychoeducation on Trauma, Grief and Cognitive-Behavioral Model; 4) Promoting Experiential Acceptance; 5) Imagined dialogue; 6) Coping Training; and two final boosting sessions. In every session, the impact of the previous consultation and evolution is evaluated.

### Treatment Fidelity

Various strategies will be employed to ensure the effective delivery of the intervention and maintain consistency among psychologists. The standardized intervention protocol for "Empower-Grief" (Coelho et al., 2024) will be utilized (manualized intervention).

The implementation team for the Empower-Grief will comprise four psychologists, all with master's degrees in clinical and health psychology and at least one year of clinical experience. This group underwent a comprehensive 20/30-hour training in the Empower-Grief intervention model. In addition to the standardized training provided to all psychologists, model sessions were conducted where experienced psychologists, each with a minimum of 10 to 15 years of clinical experience in grief intervention, demonstrated how to deliver interventions effectively. These experienced psychologists will serve as valuable resources in ensuring the fidelity and quality of intervention delivery across the team.

The implementation team of TAU will include three licensed psychotherapists or MA-level psychologists in advanced postgraduate clinical training. All therapists will have at least five years of experience and at least two years of experience working with complicated grief.

During the trial, Empower-Grief psychologists will have weekly group supervision, while TAU psychologists will have their usual practices that include team reunions to discuss cases. Ongoing supervision and monitoring of psychologists in the experimental group will include regular check-ins, feedback sessions, and opportunities for providers to seek guidance or clarification. All providers will have access to the same materials, resources, and tools required for their sessions.

Fidelity checks will be conducted to ensure quality and consistency across psychologists. Purposely constructed fidelity assessment tools will include a checklist with intended tasks, content, format, and psychologists' behaviour, completed after each session and discussed in supervision. Records will be maintained for each fidelity check, including dates, psychologist names, and fidelity assessment results, along with any corrective actions taken. The primary goal of these procedures is to ensure treatment adherence, maintain low non-participation rates, and control differential non-participation rates, particularly between follow-up times and types of termination. The expected outcomes include overall low non-participation rates, specifically in the considered conditions.

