### Statistical Analysis

To evaluate the impact of Empower-Grief relative to TAU on the primary outcome (prolonged grief symptoms) and secondary outcome (anxiety and depression), we will use a mixed-effects model. A mixed-effects model for longitudinal data (pre-post and a 6-month follow-up) accounts for the hierarchical structure of the data, with participants nested within treatment groups and the correlation between repeated measurements within subjects. The intention-to-treat principle will be followed in the analysis, ensuring that all participants randomized to each treatment condition are included in the analysis, regardless of whether they completed all assessments or adhered to the treatment protocol. To address missing data, multiple imputations will be employed, a statistical method that generates multiple plausible values for missing data points based on the observed data. This method preserves the relationships between variables and reduces the potential for bias due to missing data.

Before drawing inferences, a preliminary examination of model assumptions, including checks for the normality of residuals and homogeneity of variances, will be conducted. The primary outcome, prolonged grief severity, will be modelled using a linear mixed-effects model with fixed effects for treatment condition (Empower-Grief vs. TAU), time point (pre-treatment, post-treatment, and 6-month follow-up), and their interaction, and random effects for participants and treatment groups. Secondary outcomes, anxiety and depression symptoms, will be analyzed using similar mixed-effects models.

The sample size for this research project was estimated using G*Power software, employing a repeated measures analysis with a mixed-effects model. Assuming a low effect size of *d* = 0.25, a significance level of α = 0.05, and a power of 1-β = 0.80. With two treatment groups, Empower-Grief and treatment as usual, and measurements taken at three moments (baseline, post-treatment, and 6-month follow-up), the resulting estimated sample size for the study was 44 participants for both treatments, representing a robust size to detect the anticipated effect with high statistical power.

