To assess the predictive value of the considered predictors (i.e., posttraumatic growth, coping, attachment to the deceased, psychological flexibility, social support, and therapeutic alliance) on treatment outcomes, separate regression analyses will be conducted for each outcome measure (prolonged grief, anxiety, and depression). For each outcome, we will fit a mixed-effects model with the baseline variable as a fixed effect, adjusting for treatment condition, time, and their interaction. The random effects’ structure will remain the same as in the primary analysis.

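### The mixed model names arm rather than therapist as the level above the participant; if outcomes vary by therapist, the condition-by-time comparison will look more precise than it is

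*Protocol article*

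**What the plan says.** Treatment Fidelity describes two separate teams: "The implementation team for the Empower-Grief will comprise four psychologists", and "The implementation team of TAU will include three licensed psychotherapists or MA-level psychologists in advanced postgraduate clinical training". They differ in required experience (at least one year for Empower-Grief; at least five for TAU, two of them in complicated grief). They also differ in supervision (weekly group supervision against usual team meetings).

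Statistical Analysis claims that the mixed model "accounts for the hierarchical structure of the data, with participants nested within treatment groups". It lists fixed effects for condition, time point and their interaction, and "random effects for participants and treatment groups". The same section makes clear what the groups are: "With two treatment groups, Empower-Grief and treatment as usual". For the predictor models it adds: "The random effects’ structure will remain the same as in the primary analysis". Therapist appears neither in the model nor in the sample size paragraph.

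**The concern.** Participants seen by the same therapist may have outcomes more alike than participants seen by different therapists. The plan says that it handles the hierarchy, but the upper level it names is arm. A random effect with two levels that coincide with the fixed treatment effect cannot be told apart from that effect, and it carries no information about therapists. Participants who share a therapist are therefore analysed as independent.

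Baseline is taken before the first session (Assessments and Instruments), so a therapist can influence only the post-treatment and follow-up scores. Any therapist effect falls on the condition-by-time contrast, which is the treatment comparison, and the participant intercept does not absorb it. At stake are the standard error and p-value for prolonged grief, for anxiety and depression, and for every predictor model that inherits the same structure.

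**Working it through.** **The plan's own figures.** There is no therapist-level figure to reproduce. The only design figure is the total of 44, taken here as given. The within-subject correlation behind it is not stated, so whether 44 follows from its inputs is a separate matter on which this point does not depend.

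**Inputs from the document:** 4 and 3 therapists in separate teams; 44 participants; three measurements; α = 0.05; baseline before the first session.

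**Assumptions:** 1:1 allocation (22 + 22), because the article states block randomization without a ratio; roughly even caseloads; residual correlation 0.5 between measurements; therapist effects at post-treatment and follow-up only; therapist ICC from 0 to 0.20, because the document gives none.

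**Average caseload:** 22/4 = 5.5 in Empower-Grief; 22/3 = 7.33 in TAU.

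**Design effect** = 1 + (m − 1) × ICC. At ICC 0.05 this is 1 + 4.5 × 0.05 = 1.225 and 1 + 6.33 × 0.05 = 1.317.

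**Simulation:** 40,000 null trials per ICC, caseloads 6/6/5/5 and 8/7/7, group-by-time F test without a therapist term. The standard error ratio is for the change from baseline to post-treatment.

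| ICC (assumed) | Design effect, Empower-Grief | Design effect, TAU | True SE / model SE | Type I error (nominal 5%) |
|---|---|---|---|---|
| 0 | 1.000 | 1.000 | 1.00 | 5.1% |
| 0.01 | 1.045 | 1.063 | 1.02 | 5.5% |
| 0.02 | 1.090 | 1.127 | 1.06 | 6.3% |
| 0.05 | 1.225 | 1.317 | 1.13 | 8.2% |
| 0.10 | 1.450 | 1.633 | 1.25 | 11.3% |
| 0.20 | 1.900 | 2.267 | 1.49 | 19.0% |

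As a cross-check, the mean design effect at ICC 0.05 is (1.225 + 1.317)/2 = 1.271, and √1.271 = 1.13, which agrees with the simulated ratio. A separate simulation with a plain t-test gave 6.2%, 8.2% and 11.6% at ICC 0.02, 0.05 and 0.10.

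**With therapist respected.** A t-test on the seven therapist means has (4 − 1) + (3 − 1) = 5 degrees of freedom. Its type I error is 4.5% to 4.9% at every ICC in the table.

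**Price in power.** For an illustrative post-treatment difference of d = 0.5, the test that ignores therapist has power of about 0.37 at ICC 0. The therapist-means test has 0.26 at ICC 0, 0.21 at 0.05 and 0.19 at 0.10.

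**The case against.** **Is inflation certain?** A reader might infer that the standard errors are too small as a matter of fact. The document does not support that. It gives no therapist ICC; at zero there is no inflation and at 0.01 it is negligible. The claim is conditional on therapists differing.

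**Is therapist variation wholly confounded with arm?** A reader might infer this from the separate teams, but it is not so. Variation among therapists within each arm can be estimated, on 5 degrees of freedom, and the remedy relies on that. Only the difference between the two team averages is confounded with arm, and a therapist term does not remove it.

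**Are the therapists really nested in arm?** Treatment Conditions says that psychologists trained for each intervention will deliver both, which could be read as crossing. The separate teams, with different credentials and supervision, favour nesting. If some therapists did cross, therapist would still belong in the model.

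**Are seven therapists too few, in an exploratory trial?** This stands in part. In a one-score version of the therapist model, the variance was estimated at zero in 57%, 50% and 41% of null trials at ICC 0, 0.02 and 0.05. Overall type I error was then 3.0% to 4.5% for ICC 0 to 0.10: controlled, but conservative. The loss of power is real. However, the article still plans testing at α = 0.05 and describes its sample as robust.

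**Could an unseen analysis plan deal with it?** It could, but the article does not stay silent: it writes out the random effects and names a level that cannot do the job.

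**Conclusion.** The point holds in conditional form. The model's stated hierarchy stops at arm, where it should reach therapist within arm. If outcomes vary by therapist, the treatment comparison will be reported with too small a standard error. Under 22 per arm and even caseloads, the excess in type I error is trivial at ICC 0.01, about one percentage point at 0.02, about three at 0.05 and about six at 0.10. Uneven caseloads or a different allocation would change these figures.

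The systematic difference between the teams is a second, distinct limitation. It concerns what the effect means, and no choice of model cures it. The matter should be corrected before analysis. It does not by itself invalidate the trial.

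**What to change.** - Record the treating therapist for every participant in both arms. A reader might take this as already done, because fidelity records hold psychologist names. The article does not say that those records cover TAU or are linked to outcome data.
- Replace the random effect for treatment groups with a random effect for therapist within arm, acting on the post-baseline scores, with Kenward-Roger or Satterthwaite degrees of freedom. Carry the change into the secondary-outcome and predictor models.
- Prespecify a therapist-level sensitivity analysis, such as a comparison of therapist means, and report when the therapist variance is estimated at zero.
- State that the average difference between the teams in training, experience and supervision cannot be separated from the treatment effect, so conclusions apply to the treatments as delivered by these therapists.

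The Results section reports 44 recruited with the analysis still to come, so the model can still be changed. The work involved is one recorded variable and one substituted variance term. The statistical price is larger: wider intervals and lower power, with about 5 therapist-level degrees of freedom.
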